# High-flow Oxygen and Nitric Oxide inhalation versus high-flow oxygen alone to prevent intubation in hypoxaemic Respiratory failure (HONOR): a pilot randomised controlled trial protocol

**DOI:** 10.1186/s40814-025-01726-1

**Published:** 2025-11-26

**Keywords:** Acute respiratory failure, Endotracheal intubation, Invasive mechanical ventilation, Inhaled nitric oxide, High-flow oxygen, Oxygen therapy

## Abstract

**Background:**

When conventional oxygen therapies fail, endotracheal intubation and invasive mechanical ventilation are the current standard of care in patients with acute hypoxaemic respiratory failure. However, invasive mechanical ventilation is associated with increased hospital and intensive care length of stay, healthcare costs, and morbidity and mortality. Inhaled nitric oxide has the potential to treat hypoxaemia and potentially prevent the need for invasive mechanical ventilation.

**Aims and objectives:**

The objective of this study is to examine the feasibility and effectiveness of high-flow oxygen and nitric oxide gas inhalation compared with high-flow oxygen alone in preventing invasive mechanical ventilation for patients with acute hypoxaemic respiratory failure.

**Methods:**

In this pilot, randomised controlled feasibility study, 40 patients admitted to the intensive care unit with acute hypoxaemic respiratory failure will be randomised on a 1:1 ratio to receive one of two interventions: high-flow oxygen and nitric oxide gas inhalation (intervention) or high-flow oxygen alone (control) via high-flow nasal cannula. Feasibility, demographic, outcome, and safety data will be collected at several timepoints during participants’ admission.

**Discussion:**

This protocol outlines a structured method for investigating the effects of inhaled nitric oxide gas in preventing invasive mechanical ventilation for patients with acute hypoxaemic respiratory failure. Considering the risks, costs, and poorer outcomes associated with invasive mechanical ventilation, less invasive means of respiratory support warrant further investigation. The study will assist in planning a larger, multi-centre definitive trial.

**Trial registration:**

This study is registered on the Australian New Zealand Clinical Trials Registry (ANZCTR): ACTRN12622001411730. Registered 4th September 2022, https://www.anzctr.org.au/Trial/Registration/TrialReview.aspx?id=384881.

**Supplementary Information:**

The online version contains supplementary material available at 10.1186/s40814-025-01726-1.

## Introduction

Acute hypoxaemic respiratory failure is a common and life-threatening consequence of a diverse group of conditions [1, 2]. When conventional oxygen therapies (COT) (≤ 15 L/min oxygen via nasal prongs, cannula or mask) [3] or non-invasive ventilation (NIV) fail to correct hypoxaemia, invasive mechanical ventilation (IMV) is required. The use of IMV is common throughout the world and is increasing annually [4, 5]. Patients on IMV represent approximately 3% of acute hospitalisations and 30% of intensive care unit (ICU) admissions both internationally and in Australia [1, 2, 6–8]. However, outcomes of IMV are highly dependent on factors such as aetiology, age, co-morbidities, and severity of illness [9].

Whilst often a life-saving intervention, intubation and IMV are not without inherent risks. Risks include laryngeal injury, injury to lung parenchyma, adverse haemodynamic consequences (e.g. decreased venous return, blood pressure, and cardiac output) and predisposition to infection (e.g. ventilator-associated pneumonia (VAP)) [10–13]. Emergent endotracheal intubation also carries an especially high risk, with reported intubation-related cardiac arrest (occurring within 20 min after successful intubation) rates of up to 23% [14]. Despite evidence demonstrating a decrease in mortality rates over time, up to 30–40% of patients receiving IMV will not survive their ICU admission [15] and many survivors experience reduced quality of life, impaired physical function, and increased psychological conditions such as depression, anxiety and post-traumatic stress disorder [16, 17]. Invasive mechanical ventilation is also associated with significant increases in hospital and ICU length of stay (LOS) [6, 18], with increased cost burden ranging from 25 to 59% extra per ICU patient per day receiving IMV [7, 19, 20].

Reducing the incidence, risks, and costs associated with IMV is a major priority for healthcare providers, consumers, health system administrators, taxpayers, and policymakers [6]. By averting an artificial airway and IMV, patients with acute respiratory failure (ARF) supported with less invasive means can often avoid intravenous sedation and costly complications, such as VAP, ICU-acquired weakness, and line sepsis [6]. Avoiding intubation also facilitates patient-centric aims of early rehabilitation, speech, and oral feeding which may improve patient outcomes and reduce hospital and ICU LOS.

High-flow oxygen (HFO_2_) delivered through nasal cannula and NIV are routinely used in the treatment of ARF [21–23]. In a randomised clinical trial in patients with ARF, HFO_2_ therapy demonstrated a non-significant reduction in IMV compared with COT and NIV, however, resulted in a better 90-day survival [24]. In this study, the rates of intubation were lowest in the HFO_2_ therapy group (38%), compared with COT and NIV (47% and 50% respectively). The leading cause of intubation across groups (> 70%) was worsening ARF and hypoxaemia, warranting further investigation into the most optimal strategies to mitigate this.

The addition of inhaled Nitric Oxide (iNO) to nasal HFO_2_ may allow hypoxaemia to be corrected and potentially avoid IMV [25, 26]. As a potent vasodilator, iNO has the ability to provide selective pulmonary vascular dilation in well-ventilated sections of the lungs, improving ventilation-perfusion mismatch [26, 27]. Significant improvements in oxygenation have been demonstrated in infants with ARF on nasal continuous positive airway pressure with iNO [28]. Results within the adult population remain inconsistent, with short-term improvements in the ratio of the partial pressure of arterial oxygen (PaO_2_) to fraction of inspired oxygen (FiO_2_) ratio (PF) often being transient or not sustained [29–33]. However, the primary means of delivering iNO was either via COT or mechanical ventilation and not via nasal HFO_2_.

Literature demonstrating the effects of iNO combined with HFO_2_ (HFO_2_+iNO) in the adult population remains sparse. One multi-centre cohort study evaluated the effectiveness of HFO_2_+iNO in patients with respiratory failure from coronavirus disease (COVID-19) [34]. In this population, HFO_2_+iNO did not reduce oxygen requirements in the majority of patients. However, a subset of patients considered responders (defined as a decrease in supplemental oxygen delivered via high-flow nasal cannula (HFNC) 12 h after iNO initiation) had a trend toward decreasing need for IMV compared to non-responders [34]. Outside of this patient population, only case reports exist of the successful use of HFO_2_+iNO for preventing IMV. These reports demonstrated improvements in oxygenation within the hospital setting and maintaining safe oxygen levels during transport to and from hospital [35, 36]. Therefore, to further investigate the potential benefits of HFO_2_+iNO in preventing IMV, further research is needed in its potential to reduce the need for IMV.

## Aims

The primary aim of this pilot study is to examine the feasibility of comparing HFO_2_+iNO gas inhalation to HFO_2_ alone in patients with hypoxaemic, non-hypercapnic ARF. Several clinical outcomes (including safety and intubation rates) will also be examined. Based on the physiologic rationale [25, 37], prior investigations [28, 35, 36], and our anecdotal experience, we hypothesise that delivery of HFO_2_+iNO therapy is feasible, safe, and superior to HFO_2_ alone in preventing IMV in patients with ARF. This pilot study is a requisite initial step in exploring the proposed intervention [38] in preparation for a larger scale, multi-centre definitive trial. The feasibility and safety outcomes of the study protocol will inform future budget and protocol development whilst providing initial effect estimates to inform sample size calculation.

## Methods

### Design

This will be an open label, 1:1 parallel group, single-centre, pilot (*n* = 40) randomised controlled trial. The study protocol has been reported using the Standard Protocol Items: Recommendations for Interventional Trials (SPIRIT) statement guidelines [39], and the associated publication from the study will be reported in accordance with the CONSORT extension for randomised pilot and feasibility trials [40]. The SPIRIT figures (Figs. 1 and 2) outline the schedule of enrolment, interventions, and assessments [39].

**Fig. 1 Fig1:**
[figure not shown]
Schedule of enrolment and interventions

**Fig. 2 Fig2:**
[figure not shown]
Schedule of assessments and collection of outcomes

### Setting

This study will be conducted in a 27-bed adult ICU at a large urban Australian tertiary referral hospital specialising in cardiothoracic surgery and medicine.

### Sample size

As a pilot trial, it is not required to be powered to detect statistical significance. A sample of 40 eligible patients will be recruited over a period of 12–18 months. Assuming the proportion of patients who progress to IMV is 0.38 [24], a sample of 20 per group will produce an exact 95% CI width of 0.44.

### Recruitment and consent

Patients presenting with type I acute hypoxaemic respiratory failure (PaO_2_ < 60 mm Hg with normal or subnormal PaCO_2_) [41] will have arterial blood gas (ABG) sampling as per standard care for this patient cohort. Aligning with previous research investigating HFO_2_ in ARF [24], if the PF ratio is less than 300 mm Hg, they will be screened for suitability to participate in the study by a member of the research team. Written informed consent will be obtained from all suitable patients, their next of kin, or another substitute decision maker (SDM) as appropriate. Owing to the nature of their injury, potential participants are unlikely to have the capacity to provide written consent at the time of recruitment. Verbal consent from an SDM will be allowed if geographical or infection control visitor restrictions prevent face-to-face informed consent processes. Written consent will be sought later if a SDM is able to attend in person or are able to return a consent form provided to them via email. Should there be no SDM available initially, study procedures will be performed and consent to continue will be sought from the SDM, or the participant (should they regain capacity to consent) within a maximum of three days. Participants and/or their SDM can decline study assessments and discontinue participation at any time without explanation or penalty.

Simple random allocation will be applied, with participants allocated in a 1:1 ratio to either the control or intervention arm via a computer-generated random sequence program.

### Inclusion and exclusion criteria

Patients will need to meet all inclusion criteria and no exclusion criteria (Table 1) to be eligible to participate.

**Table 1 Tab1:** Inclusion/exclusion criteria for review

Inclusion	Exclusion
• Age ≥ 18 years • Admitted to ICU • De novo type I respiratory failure (hypoxaemia in the absence of chronic lung condition) [24] • PF ratio < 300 mm Hg • High-flow nasal cannula determined by ICU medical team to be primary method for delivery of oxygen therapy • Anticipated HFO_2_ requirement > 24 h • Arterial line in-situ for blood gas sampling • Ability to provide informed consent, or consent via a SDM	• Congenital or acquired methaemoglobinaemia reductase deficiency • Bleeding diathesis • Intracranial haemorrhage • Severe left ventricular failure • Underlying chronic respiratory failure or exacerbation of asthma (including chronic obstructive pulmonary disease (COPD) or other chronic respiratory disease) • Documented cardiogenic pulmonary oedema or acute coronary syndrome • Hypercapnic respiratory failure with PaCO_2_ > 45 mm Hg • Deterioration of neurologic status demonstrated by Glasgow Coma Scale (GCS) ≤ 12 • Urgent need for intubation (evaluated by the medical officer in charge) • Haemodynamic instability (defined by systolic arterial blood pressure < 90 mm Hg or mean arterial blood pressure < 65 mm Hg) • Use of vasopressors • Do not intubate orders • Enrolled in any other trial of targeted oxygen therapy

*ICU* intensive care unit, *HFO*_*2*_ high-flow oxygen, *Hg* mercury, *mm* millimetres, *PaCO*_*2*_ partial pressure of arterial carbon dioxide, *PF* ratio of partial pressure of arterial oxygen to fraction of inspired oxygen, *SDM* substitute decision maker

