### Blinding

Due to the nature of the interventions, participants receiving the interventions and the clinicians providing care will be aware of the treatment allocation. During the consent process, participants will be informed of the two interventions and be made aware that both are considered standard of care at the study site.

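### Eligibility does not exclude patients already on inhaled nitric oxide, which the site calls standard of care, so baseline can be on-treatment and controls can be patients whose drug was stopped

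*Protocol article*

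**What the plan says.** The Inclusion and exclusion criteria section states: "Patients will need to meet all inclusion criteria and no exclusion criteria (Table 1) to be eligible to participate". Table 1 is thus presented as the full rule, not as a selection from it.

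The relevant inclusion line is "De novo type I respiratory failure (hypoxaemia in the absence of chronic lung condition" (the bracket closes there, with a citation). The exclusions that concern treatment are use of vasopressors and "Enrolled in any other trial of targeted oxygen therapy". No line mentions iNO, whether current or recent.

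The Blinding section says that "participants will be informed of the two interventions and be made aware that both are considered standard of care at the study site". One of those two interventions is high-flow oxygen with iNO.

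The Study interventions section gives controls high-flow oxygen alone. In the other arm it starts iNO and later weans it in steps under oxygenation conditions. It does not address a participant who is already on iNO at randomisation.

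The Outcome measurements section lists change in PaO2 and in PF ratio relative to baseline, and methaemoglobin levels. The Statistical analysis section plans to explore within-group change, between-group differences and differences in rates of change with mixed models. The Aims section says the pilot will supply initial effect estimates for the sample size of a definitive trial.

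**The concern.** If iNO through high-flow cannula is usual care in this ICU, some patients may be receiving it when they are screened. Nothing in Table 1 stops them from being randomised. Two things follow for such a patient.

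- **Allocated to intervention:** the baseline already contains the drug effect. Little further change can be expected, however well the drug works.
- **Allocated to control:** study treatment is high-flow oxygen alone, so the drug goes at study start. Any change from baseline then reflects withdrawal, not the course of an untreated patient.

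The trial would then answer two questions at once: what happens when iNO is started, and what happens when it is stopped. Change from baseline in each arm would be hard to interpret. Methaemoglobin at baseline, and early on in controls, could reflect drug given before the study. The estimates meant to inform the definitive trial would carry this mixture without showing it.

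**Working it through.** **1. The plan's own figure.** The Sample size section says "Assuming the proportion of patients who progress to IMV is 0.38" and that "a sample of 20 per group will produce an exact 95% CI width of 0.44". The Clopper-Pearson interval with n = 20 gives:

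- 7 events: 0.154 to 0.592, width 0.438
- 7.6 events (exactly 0.38): 0.176 to 0.621, width 0.445
- 8 events: 0.191 to 0.639, width 0.448

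The stated 0.44 is reproduced. Nothing in this point alters it, because an added exclusion changes neither n nor the interval method.

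**2. Reading the eligibility rule.** Take a patient on iNO through high-flow cannula, with PF below 300 mm Hg, an arterial line and no chronic lung disease, who meets the remaining criteria. The patient satisfies the inclusion line as the document explains it, because that explanation concerns only chronic lung disease. No exclusion applies on account of iNO. The patient is eligible.

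**3. Effect on change from baseline.** The documents give no effect size, so let d be the effect of iNO on PF ratio. Assume it is additive, fully reversible, and the same at baseline and at follow-up. Ignore any change common to all patients. Mean changes by history are:

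| | Intervention | Control | Difference |
|---|---|---|---|
| Not on iNO at baseline | d | 0 | d |
| On iNO at baseline | 0 | -d | d |

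Let k1 of 20 intervention patients and k0 of 20 controls be on iNO at baseline. (Allocation is by simple randomisation, so 20 per arm is nominal.) Then:

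- Intervention mean change = (1 - k1/20) d
- Control mean change = -(k0/20) d
- Difference = d [1 - (k1 - k0)/20]

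The documents do not give k1 or k0. For illustration, with equal numbers in the two arms:

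| k1 = k0 (assumed) | Intervention | Control | Difference |
|---|---|---|---|
| 1 | 0.95 d | -0.05 d | d |
| 2 | 0.90 d | -0.10 d | d |
| 4 | 0.80 d | -0.20 d | d |

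Each such patient moves the arm's within-group change by 1/20 = 5% of d. With equal numbers, the two shifts cancel in the difference.

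**4. When the difference is distorted.**

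- *Chance imbalance.* Each extra pre-treated patient in the intervention arm (k1 - k0 = 1) lowers the difference by 0.05 d. Each extra one among controls raises it by 0.05 d. No stratification is described. A comparison of follow-up levels, not changes, would not be shifted in this way under the model.
- *Persistent effect.* If controls keep a share c of the drug effect after withdrawal, the difference falls by (k0/20) c d, which is 0.05 c d per pre-treated control.
- *Rebound.* If withdrawal worsens PF by an extra b beyond losing d, the difference rises by (k0/20) b, which is 0.05 b per pre-treated control.

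The documents supply no value for c or b.

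**5. Intubation within 28 days.** This outcome has no baseline value, so step 3 does not apply. For pre-treated patients, though, the arms compare continuing with stopping iNO, not adding it with not adding it.

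**The case against.** **The randomised comparison survives.** A reader might infer that carry-over biases the treatment effect. Under an additive, reversible effect it does not: the two within-arm shifts cancel, and the plan includes between-group differences. This part of the objection stands. What remains is that the plan also explores within-group change, which is shifted in any case. Cancellation also fails with persistent effect, rebound or chance imbalance.

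**The wording suggests new starts.** The Recruitment and consent section speaks of patients who present with hypoxaemic failure, and the Study interventions section describes an initial iNO setting. The standard-of-care remark is about what participants are told and does not say that iNO precedes screening. That is fair as to frequency, which is unknown. But none of these phrases is an eligibility criterion, and Table 1 is presented as the rule.

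**It is a feasibility pilot.** The primary outcome is feasibility, and the plan refrains from detailed inference. This limits the seriousness. It does not remove the stated use of the effect estimates for planning.

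**A wider reading that the documents do not support.** The hospital is a "large urban Australian tertiary referral hospital specialising in cardiothoracic surgery and medicine", and Table 1 does not mention ventilation earlier in the admission. A reader might infer that recently extubated patients turn the outcome into re-intubation, that 0.38 is the wrong planning figure, and that the definitive trial would be mis-sized. The documents do not show this:

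- They give no share of such patients and no re-intubation risk.
- They do not say whether the trial that supplied 0.38 excluded such patients. The respiratory-failure inclusion line and the PF threshold both cite that same trial.
- The 0.38 is used only for an interval width.
- Re-intubation is still progression to ventilation.
- Recording earlier ventilation, reporting by it and choosing the origin for ventilation hours belong in the case report form or the analysis plan.

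**Conclusion.** The point holds for prior iNO. As written, Table 1 admits patients already on the study drug at a site that describes the combination as standard of care, and the protocol has no handling rule for them.

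For each such patient, the arm's mean change in PF ratio is shifted by 5% of the drug effect: towards zero in the intervention arm and towards worsening in the control arm. PaO2 behaves likewise, and baseline methaemoglobin is measured on drug. The between-group difference keeps its value when the effect is additive and reversible and the arms are balanced for prior iNO, though it then mixes starting with stopping the drug. It is distorted when any of those conditions fails.

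These sizes assume 20 per arm and the simple model shown. The number of patients affected cannot be derived from the document and may be small. The harm falls on the exploratory clinical outcomes and on the estimates for the definitive trial. The feasibility criteria and the stated interval width are untouched. A general claim that the randomised comparison is biased, or that the definitive trial's sample size is wrong, would go further than the document allows.

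**What to change.** Add one exclusion to Table 1: inhaled nitric oxide during the current ICU admission before randomisation. Baseline PaO2, PF ratio and methaemoglobin are then off-drug for everyone in this respect, and change from baseline has the same meaning for every participant in an arm.

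The cost is the loss of a few candidates already on iNO. They would leave both the numerator and the denominator of the recruitment criterion, so its definition is unaffected, although accrual may be slightly slower.

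The Trial status section says recruitment had not begun at the time of writing and was planned for June 2025. If it has begun, the exclusion can be brought in by amendment with the registry update that the protocol already foresees. Prior iNO in participants already enrolled should be retrievable from the electronic medical records that the protocol uses for data collection, and their changes from baseline can be flagged.

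If the sponsor prefers to keep such patients eligible, the eligibility and Study interventions sections must be reconciled so that the protocol states what applies to a participant already on iNO. How that is managed is a clinical decision, and no rule is proposed here.

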### Blinding

Due to the nature of the interventions, participants receiving the interventions and the clinicians providing care will be aware of the treatment allocation. During the consent process, participants will be informed of the two interventions and be made aware that both are considered standard of care at the study site.

### Study interventions

Participants will receive one of two interventions: HFO_2_ alone or HFO_2_+iNO as detailed below.

High-flow oxygen (HFO2) alone (control group):

Initial FiO_2_ set at 100% with an initial flow of 60 L/minFiO_2_ will be titrated down in the first hour, targeting oxygen saturation (SpO_2_) > 92% and PaO_2_ > 60 mm HgFurther reduction in FiO_2_ every subsequent two hours maintaining SpO_2_ > 92% and PaO_2_ > 60 mm HgFlows will be reduced in increments of 10 L/min if needed for tolerance, to a minimum of 30 L/minHeated humidification to ensure delivery of HFO_2_ into the nares at a temperature set at 37 °C

High-flow oxygen and nitric oxide (HFO_2_+iNO) (intervention group):

High-flow oxygen therapy as described above, with the addition of:

iNO initially set at 20 parts per million (ppm) via HFNC by medical team, administered by ICU nursing staff, and weaned as per the following:◦After 24 h of study drug administration, wean iNO 1 ppm every 20 min or as directed by the treating ICU Consultant, provided:▪ PaO_2_ > 60 mm Hg and SpO_2_ > 92% for greater than 6 h with an FiO_2_ ≤ 50%FiO_2_ may be increased up to a maximum of 60% to compensate for any drop in oxygenation◦If nil decrement in oxygenation seen, iNO will be further weaned at a rate of 1 ppm/20 min to 0 ppm) or as directed by ICU Consultant◦If desaturation persists (SpO_2_ < 92%) for > 15 min, iNO will be returned to the most recent level prior to weaning or escalated up to a maximum of 20 ppm to maintain patient oxygenation◦iNO inhalation will be maintained if the patient in the HFO_2_ + iNO arm requires NIV

